#### **5.5.4 Withdrawal of Study Participants**

Participants may discontinue from the trial at any time at their own request, or they may be withdrawn at any time at the discretion of the Investigator or sponsor for safety, behavioural or administrative reasons. Withdrawal may be from treatment or from the whole trial. With permission all data obtained up to point of withdrawal will be used. If a participant does not return for a scheduled visit, every effort will be made to contact the participant. In any circumstance, every effort will be made to document subject outcome, if possible. The investigator will inquire about the reason for withdrawal, request that the subject return all unused investigational products, return for a final visit, if applicable, and follow-up with the subject regarding any unresolved adverse events.

If the participant withdraws from treatment then she will be unblinded and if on gabapentin she will be advised to reduce the dose according to a recognised dose reduction protocol.

If the participant discontinues from the trial and also withdraws consent for the disclosure of future information, no further evaluations will be performed and no additional data will be collected. The sponsor may retain and continue to use any data collected before such withdrawal of consent. If the participant shows signs of acute pancreatitis or falls pregnant, they will be withdrawn from treatment immediately.

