# 3 STUDY DESIGN

A two-arm parallel randomised controlled pilot trial. This will be a two centre pilot study with sites in NHS Lothian and NHS Grampian. We will recruit 60 patients over approximately nine months. After randomisation the participants will receive treatment for six months. Participants and the health care team will be unblinded at the end of their treatment.

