#### 5.5.3 Emergency Unblinding Procedures

The blinding code will only be broken in emergency situations for reasons of patient safety, where knowledge of the treatment administered is necessary for the treatment of a serious adverse event or when required by local regulatory authorities. Participants whose randomisation codes are broken will cease treatment with the study drug but will continue to be followed up. The Investigator must document the reason for breaking the blind in the participant's source documents and in the Investigator Site Master File.

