#### **6.3 DOSING REGIME**

Participants will start on 300mg gabapentin daily and will increase in 300 mg increments each week until they report a 50% pain reduction, or side effects (eg dizziness, somnolence, mood changes, appetite and poor concentration), up to a maximum dose of 2700 mgs. Patients will be advised regarding their dosing regime weekly by a member of the research team who will phone until optimum dose is reached. It will be recommended that the drug should be taken in three equally divided doses daily. Participants will be advised to remain on the maximum tolerated dose for up to 6 months. The same protocol will be used for the placebo. When the participant stops treatment then the dose will be tapered down over 7 - 10 days at the clinician's discretion.

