A further questionnaire will also be given to all participants at 6 months which will include the above and additional questions on whether they believed they were receiving Gabapentin or placebo, and also questions on acceptability of the allocation medication (and compliance) and on the acceptability of the above data collection methods. Lastly, we will ask the participants to complete a brief anonymous questionnaire once they have submitted their treatment diaries to assess level of adherence to diary keeping.

Focus groups: A purposive sample (based on age, social class and severity of symptoms) of 10 Edinburgh women (including some undergoing fMRI) and 10 Aberdeen women will be invited to participate in focus group discussions of the trial experience. Women who do not wish to participate in a focus group will be offered individual interviews using the same interview schedule. This will enable important issues arising in the focus groups to be explored in greater depth. Up to 20 interviews will be performed. Group/individual interviews will be audio-recorded, transcribed verbatim and analysed thematically to identify the issues of importance to participants.

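### The emergency-only code-break rule conflicts with routine unblinding of every woman who stops treatment, so her later questionnaires and treatment guess can be given with the allocation known

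*Protocol*

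**What the plan says.** The protocol describes unblinding in four ways.

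- **Emergency (5.5.3).** "The blinding code will only be broken in emergency situations for reasons of patient safety", to treat a serious adverse event, or on a regulator's demand. Women whose code is broken "will cease treatment with the study drug but will continue to be followed up".
- **Stopping treatment (5.5.4).** "If the participant withdraws from treatment then she will be unblinded". No emergency or other condition is attached. The same section separates stopping treatment from leaving the study: "Withdrawal may be from treatment or from the whole trial".
- **End of treatment (3 and 7.2).** "Participants and the health care team will be unblinded at the end of their treatment". Section 7.2 places this at each woman's own 6-month visit (Visit 4), listed after the questionnaire.
- **SUSARs (10.4).** Suspected unexpected serious adverse reactions are unblinded.

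Section 6.3 describes tapering when treatment stops and says "The same protocol will be used for the placebo". Section 5.5.4 discloses the allocation first and gives dose-reduction advice only to women found to be on gabapentin.

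Section 8 schedules self-completed pain, mood and quality-of-life instruments at 0, 3 and 6 months. At 6 months it adds "additional questions on whether they believed they were receiving Gabapentin or placebo". Section 9.2(ii) takes the blinding data from that 6-month questionnaire. It also plans per-protocol and intention-to-treat analyses of the Likert score to study non-compliance.

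**The concern.** The word *only* in 5.5.3 leaves no room for the routine unblinding in 5.5.4, and no cross-reference exempts 5.5.4, section 3 or 10.4. Two sites could handle the same withdrawal differently and both cite the protocol.

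The statistical consequence falls on women who stop treatment early and remain in follow-up. Their later pain and quality-of-life answers are self-reports given with the allocation known. Their answer to the treatment-belief item is then recall of what they were told, and says nothing about whether the blind held. These are also the women that the non-compliance analysis in 9.2(ii) is about. Because the trial is a pilot meant to test its methods, poor blinding data weaken what it can tell the later RCT.

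A second, smaller matter is that the health care team learns allocations one woman at a time while others are still being recruited and telephoned about dose.

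**Working it through.** **1. The plan's own figure.** Section 9.1 gives a 95% CI of 11% to 32% for 12/60. The exact (Clopper-Pearson) interval is 10.8% to 32.3%, which agrees. The figure is not disputed. It describes loss to follow-up and is not a rate of stopping treatment.

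**2. Can the unblinding rules hold together?**

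| Section | Trigger | Consistent with the emergency-only rule in 5.5.3? |
|---|---|---|
| 5.5.4 | any withdrawal from treatment | No |
| 3 and 7.2 | end of each woman's treatment | Not as worded; no exception is written |
| 10.4 | SUSAR | Only if read into the safety or regulatory grounds; no cross-reference |

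**3. Which answers can follow disclosure?**
- Woman stops before month 3 and stays in follow-up: both the 3- and 6-month questionnaires.
- Woman stops between months 3 and 6 and stays in follow-up: the 6-month questionnaire.
- In both cases the treatment-belief item is affected, because it is asked only at 6 months.
- Woman completes treatment: the 6-month questionnaire is answered blind if the Visit 4 order is kept.

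**4. How many women?** The protocol gives no stopping rate, so the rate is an assumption. Number unblinded before the final questionnaire = 60 × rate.

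| Assumed rate | Women |
|---|---|
| 5% | 60 × 0.05 = 3 |
| 10% | 60 × 0.10 = 6 |
| 20% | 60 × 0.20 = 12 |
| 30% | 60 × 0.30 = 18 |

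These counts are ceilings on the number who give open-label answers, since some of these women will also leave follow-up.

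**5. When does team unblinding start, relative to recruitment?** Inputs: section 3 ("We will recruit 60 patients over approximately nine months"; six months of treatment) and section 9.1 (about 3 to 4 women per month at each of two centres). The first completer is unblinded at about month 6. Women still to be randomised = 60 − 6 × monthly rate.
- Even accrual over nine months: 60/9 = 6.67 per month, so 60 − 40 = 20.
- 6 per month: 60 − 36 = 24 (recruitment would take 60/6 = 10 months).
- 8 per month: 60 − 48 = 12 (recruitment would take 60/8 = 7.5 months).

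**6. Does this reveal open randomisation blocks?** Randomisation is stratified by centre. In the six months between a completer's randomisation and her unblinding, her centre randomises about 6 × 3 = 18 to 6 × 4 = 24 further women. Unless blocks are about that large, hers has closed.

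**The case against.** The strongest reply is that 5.5.3 is headed as an emergency procedure and was never meant to govern planned disclosure at the end of treatment or on withdrawal. That is a plausible intention, but the wording is absolute and nothing in the text states the exception. The textual conflict therefore stands, though it is easy to repair.

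Several stronger readings are tempting, and the protocol does not support them:

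- **Final data become open-label across the trial.** They do not. Visit 4 lists the questionnaire before unblinding, and telling the team about one woman does not unblind another woman's self-report.
- **Staff can predict the next allocation.** At 3 to 4 women per month per centre, a completer's block has almost certainly closed by her month 6. Randomisation is also web-based with varying block sizes. Only a very early stopper could reveal anything about an open block.
- **The second primary endpoint is biased.** Section 2.2.1 already counts a woman as failing if she does not take all her medication, so learning her arm after stopping cannot change that result.
- **Twelve women are known to be affected.** The 12/60 in 9.1 concerns loss to follow-up, and women lost to follow-up give no final data.
- **A bias of a given number of points can be stated.** Stoppers in both arms are unblinded, so net bias depends on the size and direction of any shift in each arm. The protocol gives neither.

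It is also fair to say that the health care team in section 3 may not be the research team that recruits (5.1) and telephones (6.3). The protocol does not settle this, so the staff-awareness concern is conditional on some overlap.

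**Conclusion.** The concern holds in limited form. Section 5.5.3 conflicts with 5.5.4, and sections 3, 7.2 and 10.4 add routes that it does not allow for; this is plain from the text. Early stoppers who stay in follow-up can give pain, quality-of-life and treatment-belief answers after disclosure. That makes the blinding assessment uninformative for them and mixes blinded and open-label reports in the intention-to-treat Likert analysis.

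The size is 3 to 18 of 60 women unblinded before their final questionnaire, resting wholly on an assumed stopping rate of 5% to 30%. Completers' main 6-month data are safe provided the Visit 4 order is followed.

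Team unblinding starts at about month 6, with roughly 12 to 24 women still to be randomised. The issue there is staff awareness while others are recruited and phoned, if the teams overlap.

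The analyses affected are secondary ones in a small pilot. The change is worth making because blinding is one of the things this pilot is meant to assess.

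**What to change.** 1. Reconcile sections 3, 5.5.3, 5.5.4, 6.3, 7.2 and 10.4 so that each unblinding route is named once, with who is told and when. How stopping and dose reduction are handled clinically is for the sponsor and investigators to settle in that reconciliation; no position is taken here.
2. For non-emergency withdrawal from treatment, take the questionnaire and the treatment guess at the withdrawal contact, before the allocation is disclosed. Exempt emergency and SUSAR code breaks.
3. State that the listed Visit 4 order, questionnaire then unblinding, is mandatory.
4. Where feasible, keep staff who recruit, phone and collect outcomes unaware of individual allocations until the last 6-month questionnaire is in. Say whether the health care team in section 3 includes them.
5. Record the date of every disclosure, and use only pre-disclosure answers in the blinding assessment. The date lets the Likert analysis identify answers given after disclosure.

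The cost is protocol wording, a short extra questionnaire at a contact that 5.5.4 already foresees, and the small inconvenience of routing disclosure around the research staff.

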### **6 INVESTIGATIONAL MEDICINAL PRODUCT AND PLACEBO**

#### **6.1 STUDY DRUG**

##### **6.1.1 Study Drug Identification**

Gabapentin 300 mgs hard capsule

Placebo

##### **6.1.2 Study Drug Manufacturer**

Actavis UK Limited

##### **6.1.3 Marketing Authorisation Holder**

Actavis UK Limited

[name]

Barnstaple

[name]

##### **6.1.4 Labelling and Packaging**

Packaging and labelling of the over-encapsulated gabapentin and placebo will be carried out by:

Bilcare GCS (Europe) Ltd.

[name]

[name]

[name]

UK

##### **6.1.5 Storage**

The medicinal product should be stored at room temperature not above 25°C

##### **6.1.6 Summary of Product Characteristics or Investigators Brochure**

The Summary of Product Characteristics (SmPC) is given in Appendix 1.

#### **6.2 PLACEBO**

The placebo will be manufactured, labelled and packed by Bilcare GCS (Europe) Ltd

#### **6.3 DOSING REGIME**

Participants will start on 300mg gabapentin daily and will increase in 300 mg increments each week until they report a 50% pain reduction, or side effects (eg dizziness, somnolence, mood changes, appetite and poor concentration), up to a maximum dose of 2700 mgs. Patients will be advised regarding their dosing regime weekly by a member of the research team who will phone until optimum dose is reached. It will be recommended that the drug should be taken in three equally divided doses daily. Participants will be advised to remain on the maximum tolerated dose for up to 6 months. The same protocol will be used for the placebo. When the participant stops treatment then the dose will be tapered down over 7 - 10 days at the clinician's discretion.

#### **6.4 DOSE CHANGES**

See above. If side effects prevent escalation of the dose one week then participants will be advised to try and increase the drug the following week.

#### **6.5 PARTICIPANT COMPLIANCE**

All participants will be given a diary at randomisation and asked to document daily drug use (including self-medication and alternative treatments, eg acupuncture), side effects, reasons for drug escalation or reduction. We will also include specific healthcare resource use questions (e.g. attendance at GP, hospital). We will record the proportion of participants who completed their diaries with no missing data.

## 6.6 OVERDOSE

Acute, life-threatening toxicity has not been observed with gabapentin overdoses of up to 49g. Symptoms of overdose include dizziness, double vision, slurred speech, drowsiness, lethargy, and mild diarrhoea. All patients have recovered fully with supportive care. Reduced absorption of gabapentin at higher doses may limit drug absorption at the time of overdosing and, hence, minimize toxicity from overdoses.

Although gabapentin can be removed by haemodialysis, based on prior experience it is usually not required. However, in patients with severe renal impairment, haemodialysis may be indicated.

An oral lethal dose of gabapentin was not identified in mice and rats given doses as high as 8000 mg/kg. Signs of acute toxicity in animals included ataxia, laboured breathing, ptosis, hypoactivity, or excitation.

## 6.7 OTHER MEDICATIONS

### 6.7.1 Non-Investigational Medicinal Products

#### 6.7.2 Permitted Medications

Participants may take the following concomitant medications during the course of the study, but those other than pain and anti-emetic medications must have been used at a stable dose for 30 days or more prior to randomisation.

| Class of allowable (with restrictions) medication |                              | Examples (not comprehensive list)                                                                                      | Allowable treatment dose                                                                                                                                                                                                                   |
|---------------------------------------------------|------------------------------|------------------------------------------------------------------------------------------------------------------------|--------------------------------------------------------------------------------------------------------------------------------------------------------------------------------------------------------------------------------------------|
| Medication used for pain relief                   | Analgesics                   | Oral paracetamol (acetaminophen)                                                                                       | Maximum dose of paracetamol or any paracetamol-containing products $\leq 4$ g/day (8x500 mg/day)                                                                                                                                           |
|                                                   | Anti-inflammatory            | Aspirin
OTC NSAID ibuprofen, diclofenac,
Stable inhaled corticosteroids                                          | $\leq 325$ mg/day for prophylaxis use only (as antithrombotic agent).
Per product label                                                                                                                                                 |
|                                                   | Opioids                      | Oxycodone
Codeine
Dihydrocodeine
Morphine
Methadone
Tramadol
Fentanyl
Buprenorphine
Tapentadol | Per product label
Anyone given morphine will be carefully observed for signs of CNS depression, eg somnolence, and the dose of gabapentin or morphine will be reduced appropriately. Morphine will only be given on an inpatient basis. |
|                                                   | Non-harmacological therapies | Physical therapy, massage, chiropractic care, psychological care, exercise, yoga, medication                           |                                                                                                                                                                                                                                            |
|                                                   | Local anaesthetics           | Topical lidocaine                                                                                                      | Per product label                                                                                                                                                                                                                          |
| Medication used for mood disorders                | Anti-depressants             | SSRIs including citalopram, fluoxetine, fluvoxamine, paroxetine, sertraline                                            | Per product label                                                                                                                                                                                                                          |
|                                                   | Sedative                     | Midazolam/temazepam                                                                                                    | Per product label                                                                                                                                                                                                                          |
| Medication used for control of nausea/vomiting    | Anti-emetics                 | 5HT-3 antagonists are strongly recommended for use at the start of surgery

H1 (dimenhydrinate)                  | Per product label                                                                                                                                                                                                                          |

|                              |                  |                             |                                                                                      |
|------------------------------|------------------|-----------------------------|--------------------------------------------------------------------------------------|
| Medication used for insomnia | Hypnotics        | Zopiclone                   | 3.75-7.5 mgs/night. Intermittent use for insomnia only, no more than 3 doses a week. |
|                              |                  | Zolpidem                    | 5-10 mg/night. Intermittent use for insomnia only, no more than 3 doses a week.      |
|                              |                  | Zaleplon                    | 5-10 mg/night. Intermittent use for insomnia only, no more than 3 doses a week       |
|                              | Benzo-diazepines | Temazepam, triazolam        | Intermittent use for insomnia only, no more than 3 doses a week.                     |
|                              | Antihistamines   | Diphenhydramine, doxylamine | Intermittent use for insomnia only, no more than 3 doses a week.                     |

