### 4.3 EXCLUSION CRITERIA

- Known pelvic pathology eg endometriosis, cyst
- Taking gabapentin or pregabalin or any restricted medications
- Due to undergo surgery in the next 6 months
- History of renal impairment
- Allergic to gabapentin
- Breast feeding
- Pregnancy or planning pregnancy in the next 6 months

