### 6.7.3 Prohibited Medications

Prohibited from randomisation

| Class of prohibited medications                |                                                                    | Examples
(not comprehensive list)                                                                                                                                                                                                                                                                                           | Minimum washout periods prior to study medication dosing             |
|------------------------------------------------|--------------------------------------------------------------------|--------------------------------------------------------------------------------------------------------------------------------------------------------------------------------------------------------------------------------------------------------------------------------------------------------------------------------|----------------------------------------------------------------------|
| Anxiolytics, sedative hypnotics                | Benzo-diazepines                                                   | Alprazolam, clonazepam, diazepam, flurazepam, lorazepam, quazepam, triazolam, temazepam (see table above for allowed and intermittent use for insomnia)                                                                                                                                                                        | ≥7 days                                                              |
| Used for pain or may confound pain measurement | Barbiturates/
barbiturate combinations/
belladonna alkaloids | Amobarbital, butabarbital, metharbital, pentobarbital, phenobarbital, secobarbital, atropine sulfate, hyoscyamine sulfate, scopolamine hydrobromide, antrocol (atropine and Phenobarbital) butibel (belladonna and butabarbital), donnatal (atropine sulfate, hyoscyamine sulfate, scopolamine hydrobromide and Phenobarbital) | ≥7 days                                                              |

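### The per-label sedative entry for midazolam and temazepam in section 6.7.2 conflicts with the insomnia limit and the benzodiazepine prohibition, and the medication exclusion in section 4.3 names no table

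*Protocol*

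**What the plan says.** Temazepam appears in three rows of the two medication tables, and midazolam in one.

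- Section 6.7.2, mood disorders, sedative row: "Midazolam/temazepam" is permitted at the product-label dose. The protocol adds no limit on frequency.
- Section 6.7.2, insomnia, benzodiazepine row: temazepam and triazolam are permitted, with the condition "Intermittent use for insomnia only, no more than 3 doses a week".
- Section 6.7.3, under the class "Anxiolytics, sedative hypnotics": benzodiazepines are prohibited from randomisation with a washout of at least 7 days before dosing. The examples end with "triazolam, temazepam (see table above for allowed and intermittent use for insomnia", which sends the reader back to section 6.7.2. The list of examples is stated not to be complete.

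The introduction to section 6.7.2 adds that permitted drugs, other than those for pain and nausea, "must have been used at a stable dose for 30 days or more prior to randomisation".

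Eligibility is tied to medication mainly by one line in section 4.3: "Taking gabapentin or pregabalin or any restricted medications". The permitted table is headed "Class of allowable (with restrictions) medication". The table in section 6.7.3 is headed as prohibited.

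**The concern.** A site that reads the sedative row alone may let a participant take temazepam or midazolam throughout the trial as the label allows. A site that reads section 6.7.3 would have the same drug stopped before dosing and kept out, apart from the limited insomnia use of temazepam. These instructions govern a sedative taken alongside a study drug for which section 6.3 lists dizziness and somnolence as side effects, so the conflict bears on participant management as well as on eligibility.

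The wording of section 4.3 is a second, smaller fault. An exclusion criterion should tell the screener which list to check. This one uses a term that no table carries and that most resembles the heading of the list of allowed drugs.

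**Working it through.** **The plan's own figure.** Section 9.1 gives a 95% interval of 11% to 32% for 12 of 60 women lost to follow-up. The exact (Clopper-Pearson) interval for 12/60 is 10.8% to 32.3%, which rounds to the stated figure. Neither 60 nor 12 depends on the medication tables, so this figure is not at issue. The rest of the check compares the text.

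**Step 1: the three rows side by side.**

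| Place | Drugs | Rule |
|---|---|---|
| 6.7.2, mood disorders, sedative | midazolam, temazepam | permitted, per label, no frequency cap |
| 6.7.2, insomnia, benzodiazepines | temazepam, triazolam | permitted, intermittent, at most 3 doses a week |
| 6.7.3, anxiolytics and sedative hypnotics, benzodiazepines | the class; eight drugs named, temazepam and triazolam among them | prohibited from randomisation, washout at least 7 days, with a reference back to 6.7.2 for insomnia |

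**Step 2: compare them in pairs.**

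- Insomnia row and prohibited row: consistent. The prohibited row carries its own exception for this use.
- Sedative row and prohibited row: in conflict on their face. One permits a benzodiazepine as a sedative; the other prohibits benzodiazepines under a class that includes sedatives. The exception is worded around insomnia, whereas the sedative row sits under mood disorders.
- Sedative row and insomnia row: one sets no frequency cap, while the other confines temazepam to intermittent use, at most 3 doses a week, for insomnia only. The label is not reproduced in the protocol, so how far the two differ in practice cannot be read from it.
- Midazolam: it is named only in the sedative row. As a benzodiazepine it falls under the prohibited class, whose list is not exhaustive. It is absent from the insomnia row, so the exception does not reach it.

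**Step 3: a test case.** Take a woman who has used temazepam as a sedative, per label, at an unchanged dose for at least 30 days before randomisation. By the introduction and sedative row of section 6.7.2 she may continue during the study. By section 6.7.3 she must have been off it for at least 7 days before dosing and may not resume it for that use. Both cannot be followed. With midazolam in place of temazepam the result is the same, and the insomnia exception is not even arguable.

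**Step 4: the term in section 4.3.** Three readings are possible.

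- It means the table in section 6.7.3. This fits the rest of the protocol.
- It means the table in section 6.7.2, because that heading speaks of restrictions. This fails. The introduction to that section lets participants take the listed drugs, section 5.5.2 allows other medication including analgesics, and section 8 lets permissible pain medication start at any time.
- It means both tables, because section 8 refers to the permissible and excluded lists together as restrictions. This fails for the same reasons.

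The first reading is therefore the likely intent, but it has to be inferred. Even then, whether a woman using temazepam as a sedative is excluded comes back to the conflict in step 2.

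**The case against.** The permitted table is organised by indication, so different limits for mood disorder and for insomnia need not contradict each other. The cross-reference in section 6.7.3 can also be read more widely, its word for allowed use covering the sedative row and its word for intermittent use covering the insomnia row. This has some force. It is why the sedative row is best described as not clearly reconciled. It does not settle the matter: the phrase ends on insomnia, the insomnia row itself says only, and midazolam is not mentioned in either place. An instruction that needs this much interpretation should be rewritten.

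A reader might infer a three-way contradiction, with temazepam freely allowed, allowed intermittently and prohibited. The protocol does not support that, because the second and third entries are joined by the cross-reference. A reader might also infer that section 4.3 excludes women taking listed analgesics. Sections 5.5.2, 6.7.2 and 8 rule that out, and a site reading the whole protocol would not exclude someone for taking paracetamol.

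Finally, section 5.4 collects current medication and the reason for not entering randomisation, and section 8 keeps a log with reasons for non-recruitment. Exclusions on medication grounds could therefore be reviewed afterwards. That stands for the recruitment data. It does not help staff who must advise a participant during treatment.

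**Conclusion.** The concern holds in a narrow form. One row, the per-label sedative entry for midazolam and temazepam, conflicts with the benzodiazepine prohibition and with the insomnia limit, and one exclusion term is undefined. It is an inconsistency of wording that bears on eligibility and on sedative use during treatment. It deserves correction because the correction is specific and cheap.

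No effect on the first primary endpoint, the proportion of eligible women randomised, is shown. A reader might infer one from section 9.1: 6 to 7 laparoscopies a month × 2 centres × 9 months gives 108 to 126 women, so 60 randomised would be 60/126 = 47.6% to 60/108 = 55.6%, on either side of the >50% criterion in section 9.2. A few reclassified women might then seem to decide the result. The documents do not support that step:

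- The 108 to 126 are laparoscopies that fit the inclusion criteria. Exclusions have not been shown to be applied, and section 4.2 accepts laparoscopies up to 3 years old, so this is not a count of eligible women.
- The number of women taking the disputed drugs is not given.
- The direction depends on who is removed. Suppose, purely for illustration, a pool of 120 from which 6 are reclassified. With the numerator held fixed, 60/120 = 50.0% becomes 60/114 = 52.6%. If those 6 were recruited at the same rate as the others, 3 leave the numerator as well, giving 57/114 = 50.0% and no change.
- A woman who completes the washout may become eligible, which reduces any effect.

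The conclusion rests on the text alone, on midazolam belonging to the prohibited class, and on the likely but unstated intent that section 4.3 refers to section 6.7.3.

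**What to change.** Reconcile the sedative row of section 6.7.2 with the insomnia row and with section 6.7.3, so that temazepam and midazolam each have one stated rule and the cross-reference in section 6.7.3 points to every permitted use it is meant to except. Which rule stands is for the clinical team. In section 4.3, replace the undefined term with a reference by name and number to the table that excludes.

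The cost is a protocol wording amendment, with the approvals that section 14.1 requires, and a note to both centres. No sample size, interval or analysis needs to be recalculated.
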